**Table 1 Tab1:**
[figure not shown]
Schedule of enrolment, intervention, and assessments according SPIRIT figure

BRIC Bereavement in Relatives in the Intensive Care; −t_1_ Approach and enrolment of cohort 1; −t_1_ Approach and enrolment of cohort 2; t_0_ Baseline measurement; t_1_ 6 to 8 weeks post-loss; t_2_ 6 months post-loss; TGI-SR Traumatic Grief Inventory-Self Report Version’; HADS Hospital Anxiety and Depression Scale; IES-R ‘Impact of Events Scale-Revised’; CQI R-ICU ‘Consumer Quality Index Relatives in the ICU’; QODD ‘The Quality of Dying and Death questionnaire’

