#### Multicomponent nurse-led bereavement support intervention

Based on existing (inter) national policies, facilities and evidence-based practices [34], we aim to develop a nurse-led support intervention with subsequent implementation in practice during the study period. This intervention is expected to include 1) communication strategies, such as an information leaflet on loss and grief [21], a condolence greeting card [35], and a checklist with relevant topics to discuss in the process of dying and death [26]; 2) materials to make a keepsake [32], such as a lock of hair and a fingerprint; and 3) a nurse-led follow-up service, such as a memorial meeting and telephone follow-up calls 4 months post-loss [36]. The intervention will be developed in a multidisciplinary collaboration, including intensivists, spiritual service and social workers. The nurses will be invited to extend the standard of care with elements of the intervention applied to the needs and values of the relatives, thus providing personalized bereavement support. This multicomponent nurse-led intervention will be developed in co-creation with bereaved relatives to maximize care according to their ideals and perspectives, and not solely built on professional beliefs. Therefore, the Dutch foundation ‘Family and patient Centered Intensive Care’ (FCIC) will be involved in the development process.

To strengthen the development and implementation of the intervention fidelity measures will be used which will help to understand whether planned intervention was effective [37]. Several methods can be used assessing the quality and include both acceptability of measures in relation to the needs of the stakeholders (bereaved relatives) and practicality of the measures in relation to applicability for the users (ICU professionals). The implementation evaluation of this complex intervention will be performed by applying the RE-AIM model; Reach, Efficacy, Adoption, Implementation and Maintenance. The RE-AIM model is an instrument that measures the total impact of an intervention and provides insight into causes for (in)efficacy. RE-AIM is widely used in public health research, and will support the applicability and dissemination of the study results [38]. Table 2 provides an overview of the RE-AIM model applied in the current study.

**Table 2 Tab2:** Overview of the RE-AIM model applied in the BRIC study

RE-AIM	Characteristics	Level	Data collection

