#### Study cohorts and time points

Both cohorts will be performed in study samples of 200 relatives per group, all participants will be invited to complete questionnaires measuring complicated grief, anxiety, depression and posttraumatic stress. Cohort 1 includes all reported first and second contact persons of patients who died in the ICU in 2018, which will serve as a pre-intervention baseline measurement. Eligible relatives were approached from March to May 2019 (−t_1_) and participants received the questionnaires directly after they signed the consent form (t_0_). The intervention was conducted from June 2019 onwards. Cohort 2, including all bereaved relatives in the ICU from October 2019 until March 2020, will serve as a post-intervention follow-up measurement. Eligible relatives will be approached 12 weeks after the death of their loved one (−t_2_) and participants will receive the questionnaires directly (t_1_) and at 6 months (t_2_) after they signed the consent form. The study design and timeline is presented in Fig. 1. For each deceased patient, up to 3 relatives can be included in the study. This recruitment process has been shown feasible in a previous study [39].

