**Fig. 1 Fig1:**
[figure not shown]
BRIC study design. BRIC Bereavement in Relatives in the Intensive Care; t_0_ baseline measurement; t_1_ 6 to 8 weeks post-loss; t_2_ 6 months post-loss; TGI-SR Traumatic Grief Inventory-Self Report Version’; HADS Hospital Anxiety and Depression Scale; IES-R ‘Impact of Events Scale-Revised’; CQI R-ICU ‘Consumer Quality Index Relatives in the ICU’; QODD ‘The Quality of Dying and Death questionnaire’; RE-AIM model; Reach, Efficacy, Adoptation, Implementation and Maintenance

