#### Statistical analysis

Power and feasibility: Baseline (retrospective; t_1_) and follow-up measurements (6 weeks; t_2_ and 6 months; t_3_) will be performed in study samples of 200 relatives per group. These numbers are feasible, starting from a mean of 325 ICU deaths each year in the study setting, given a (2x) 12-month inclusion period, an expected 1.5 loved one per death, and an expected inclusion rate of 50% at 6 weeks and a retention rate of 80% at 6 months. These numbers ensure an effect size of 0.5 with a GPower t-test for the ´difference between two independent means´ (1-β = 95%, *p* < .05, two-tailed, d = .5) [48].

Analyses: Descriptive statistics (e.g., means, medians, or proportions as appropriate) and Student’s T-test between pre-post groups on demographic variables (e.g., gender, age, educational level) and outcome measures (e.g., complicated grief, anxiety, depression, posttraumatic stress, experiences with care) will be used to present noticeable differences between the baseline and intervention groups. Missing data will be handled using the multiple imputation. The scores will be analysed based on original data, and when available, according to established cut-offs. All test will be bilateral and significance will be defined as *p* < .05.

To test the hypotheses repeated measure analyses of variance (ANOVA) will be conducted with time as the within-subject factor (pre- versus post-intervention) and group (cohort 1 and 2) as the between-subject factor. Cohen’s d will be calculated to present effect sizes if applicable. Hierarchical regression analyses will be performed to explore determinants and identify subgroups (such as gender, ethnicity, risk profiles, relationship with patient) of bereaved relatives in the ICU who are at particular risk of developing mental health problems (i.e., those with scores above established cut-offs). Covariates, such as reason of admission, severity of illness, cause of death, bereavement care, time to say goodbye and social support, will be included in the regression model. This model will be adapted for cluster effects to correct for multiple relatives per deceased patient.

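### Cohort 2's measurement times contradict each other, by at least 4–6 weeks at t1 and about 2.8 months at t2, so the plan does not fix when the primary outcome is measured

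*Protocol article*

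**What the plan says.** All places are in the protocol article.

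- **Study cohorts and time points**, on cohort 2: "Eligible relatives will be approached 12 weeks after the death of their loved one", and then "participants will receive the questionnaires directly (t_1_) and at 6 months (t_2_) after they signed the consent form". Cohort 1 covers deaths in 2018; its relatives were approached from March to May 2019 and measured once.
- **Legends of Table 1 and Fig. 1**: "t_1_ 6 to 8 weeks post-loss; t_2_ 6 months post-loss".
- **Statistical analysis**, power paragraph: "Baseline (retrospective; t_1_) and follow-up measurements (6 weeks; t_2_ and 6 months; t_3". The feasibility reasoning assumes "an expected inclusion rate of 50% at 6 weeks and a retention rate of 80% at 6 months".
- **Multicomponent nurse-led bereavement support intervention**: the third component is a nurse-led follow-up service. Its examples are a memorial meeting, for which no date is given, and "telephone follow-up calls 4 months post-loss". The Hypotheses section counts this service as part of the intervention.
- **Long-term grief in bereaved relatives**: the disorder is described by symptoms that persist beyond 6 months after the loss.
- **Primary outcomes**: complicated grief on the TGI-SR, rated over the preceding month, with no measurement time attached.

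**The concern.** The primary outcome is a symptom score, and the cohorts are not randomised. Time since the death is therefore part of what is being compared. If the sections disagree on when cohort 2 is measured, two readers who follow the article faithfully would collect different data and estimate different contrasts with cohort 1.

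The choice between t1 and t2 matters too. As scheduled, t1 comes before the follow-up calls are due and before the duration that the protocol uses to describe the disorder. An effectiveness claim resting on t1 would concern an intervention still in progress and an outcome not yet mature.

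**Working it through.** One month is taken as 30.4375 days.

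**1. The plan's own figure.** Using the stated annual deaths, relatives per death, inclusion and retention, and taking the 12-month inclusion period at face value:

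325 × 1.5 × 0.50 = 243.75 included; 243.75 × 0.80 = 195 retained.

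This agrees with the planned 200 per group. The 50% inclusion rate, however, is placed at 6 weeks. If first contact is at 12 weeks, nobody can be included at 6 weeks, so that rate belongs to a time that does not occur. The documents give no inclusion rate at 12 weeks. As an illustration only, 40% would give 325 × 1.5 × 0.40 × 0.80 = 156 and 60% would give 234.

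**2. The schedules side by side.**

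| Source | First measurement after the death | Later measurement |
|---|---|---|
| Cohort section | t1: from 12 weeks (84/30.4375 = 2.8 months) | t2: 6 months after consent |
| Table 1 and Fig. 1 legends | t1: 6–8 weeks after the death | t2: 6 months after the death |
| Power paragraph | called t2: 6 weeks | called t3: 6 months |

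In the power paragraph, t1 is the retrospective baseline, which the legends call t0.

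**3. Gap at t1.** 12 − 8 = 4 weeks and 12 − 6 = 6 weeks. These are minima, because consent must be signed and returned after the approach.

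**4. Gap at t2.** With prompt consent, 2.8 + 6 = 8.8 months after the death (12 + 26.1 = 38.1 weeks), against 6.0 months (26.1 weeks). The gap is about 2.8 months, and longer if consent is slow.

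**5. Position relative to the calls.** Four months is 4 × 30.4375/7 = 17.4 weeks.

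- Legends: t1 is 17.4 − 8 = 9.4 to 17.4 − 6 = 11.4 weeks before the calls.
- Cohort section, prompt consent: t1 is 17.4 − 12 = 5.4 weeks before them.
- t2 follows the calls under either anchor (26.1 or 38.1 weeks).

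**6. Cohort 1.** The shortest interval from death to approach is 31 December 2018 to 1 March 2019: 60 days, or 2.0 months. The longest is 1 January 2018 to 31 May 2019: 515 days, or 16.9 months. Both candidate times for t2 (6.0 and 8.8 months) lie inside this range. A t1 at 6–8 weeks (42/30.4375 = 1.4 to 56/30.4375 = 1.8 months) lies below it.

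**The case against.** Several points on the other side have weight.

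- **The calls are an example.** The intervention section describes what is expected and illustrates it. The memorial meeting carries no date. A reader might infer that the third component is wholly missing at t1 for every relative in cohort 2, under any schedule. The documents do not support that. Consent returned more than about 5.4 weeks after a 12-week approach would put t1 after the calls. Study status also reports that cohort 2 recruitment was postponed. If the death window to 31 March 2020 stood and recruitment had not begun by publication on 18 August 2020, even the latest death was 140 days (4.6 months) past. What stands is narrower: as scheduled, t1 comes before the planned calls.
- **The full intervention can still be tested.** t2 follows the calls under either anchor, and the Discussion states that following change over time is a purpose of the study. An early measurement is legitimate; the limit is on what it can be used to claim.
- **Multiplicity.** A reader might infer two separate 5% tests of the primary outcome, at t1 and at t2. The Statistical analysis section does not state that. It gives a general significance threshold, descriptive t-tests and a repeated-measures ANOVA. Handling of multiplicity may sit in an analysis plan that is not shown, so no error-rate claim is made here.
- **The t2 anchor.** The cohort sentence could be read with the consent clause attached only to the immediate questionnaire. The plain reading is otherwise, and the 2.8-month gap depends on it. The t1 contradiction does not.
- **Does timing matter for grief?** The French multicentre study cited in the Background found complicated grief unchanged between 6 and 12 months, while posttraumatic stress fell from 44% to 36%. That softens the concern about 6 against 8.8 months for the primary outcome. It does not do so for the secondary outcome, and it says nothing about times before 6 months.
- **The outcome is a severity score.** The TGI-SR yields a score and a risk category, not a diagnosis of the disorder. An early score is therefore interpretable as early severity, though not as persistent grief.

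**Conclusion.** The contradiction holds. First contact at 12 weeks is incompatible with a questionnaire at 6–8 weeks or 6 weeks, whatever the missing figures show, because the legends state the times in words. The size is at least 4–6 weeks at t1. At t2 it is about 2.8 months, given the plain reading of the cohort sentence and prompt consent. The shifted labels add to the confusion, since t1 and t2 denote different measurements in different sections.

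This is more than clerical. It decides when the primary outcome is measured, and the inclusion assumption is tied to one of the conflicting times. As scheduled, t1 is not suited to carry the effectiveness claim; t2 can. The point should be settled before cohort 2 is recruited, which Study status says had not yet started.

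**What to change.** 1. Reconcile the cohort section, both legends and the power paragraph to one schedule, with every cohort 2 measurement counted from the date of death, an allowed window, and one set of labels. Say how the postponed recruitment affects it.
2. Restate the inclusion assumption at the reconciled first time point, and rework the feasibility figure from it.
3. Name t2, at one fixed time not before 6 months after the death, as the primary effectiveness comparison on the TGI-SR. Report t1 as early course.
4. Include time since loss as a covariate in the comparison with cohort 1. Fixing cohort 2's times alone does not match the cohorts, because cohort 1 was approached about 2–17 months after the death. Cohort 2 will have little spread in time at t2, so the adjustment will rest largely on the relation seen in cohort 1. That should be stated as an assumption.

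The cost is protocol wording and one added covariate. The downside is that no early effectiveness claim can be made at t1.

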**Fig. 1 Fig1:**
[figure not shown]
BRIC study design. BRIC Bereavement in Relatives in the Intensive Care; t_0_ baseline measurement; t_1_ 6 to 8 weeks post-loss; t_2_ 6 months post-loss; TGI-SR Traumatic Grief Inventory-Self Report Version’; HADS Hospital Anxiety and Depression Scale; IES-R ‘Impact of Events Scale-Revised’; CQI R-ICU ‘Consumer Quality Index Relatives in the ICU’; QODD ‘The Quality of Dying and Death questionnaire’; RE-AIM model; Reach, Efficacy, Adoptation, Implementation and Maintenance

#### Primary outcomes

Complicated grief will be measured with the Dutch version of the ‘Traumatic Grief Inventory-Self Report Version’ (TGI-SR), 18 items [40]. Respondents are asked to rate the extent to which they experienced the 18 symptoms listed during the preceding month on a 5-point scale: 1 = ‘never,’ 2 = ‘rarely,’ 3 = ‘sometimes,’ 4 = ‘frequently,’ and 5 = ‘always’. The TGI-SR demonstrated strong internal consistency, Cronbach’s alpha = .95. A total TGI-SR score, providing an index of the severity of potentially problematic grief, can be obtained by summing the 18 items. A total symptom severity score (range 17–85) can be obtained by summing the scores for items 1–11 and 13–18. Elevated scores (tentatively, a cut-off score of ≥61 meets the criteria for a provisional diagnosed grief disorder) correlate significantly with elevated scores on indices of psychopathology and lower quality of life, attesting to the concurrent validity [40]. Therefore, in our study, the risk of complicated grief will be categorized as ‘low risk’ (17 to 60) or ‘high risk’ (≥ 61).

#### Secondary outcomes

Anxiety and depression; measured with the Dutch version of the ‘Hospital Anxiety and Depression Scale’ (HADS), that includes to 7 items on the subscales tapping ‘Anxiety’ and ‘Depression’ respectively [41, 42]. These subscales are reliable and valid measures of mental health status with items concerning symptoms of psychological well-being. Scores range from 0 to 21, categorized as ‘normal’ (0 to 7); ‘mild’ (8 to 10); and ‘moderate to severe’ (11–21).Posttraumatic stress; measured with the 21-item Dutch version of the ‘Impact of Events Scale-Revised’ (IES-R) [43]. This measuring instrument is used worldwide to self-report the frequency of intrusive and avoidant phenomena after a variety of traumatic experiences. The reliability of the Dutch version of the IES is adequate across the various stressors [44]. Scores range from 0 to 88, categorized as ‘low risk’ (0 to 11); ‘moderate risk’ (12 to 32); and ‘high risk’ (≥ 33).Experiences with care; measured with items derived from the ‘Consumer Quality Index Relatives in the ICU’ (CQI R-ICU) [45] and ‘The Quality of Dying and Death questionnaire’ (QODD) [46, 47], includes 30 items in total. Both instruments have been developed and validated in Dutch, and report high internal consistency reliability and construct validity. The subscales measure aspects of communication, quality of dying and death, and quality of support to relatives.Questions to evaluate which intervention elements were actually received and how they were appreciated will be added to the questionnaires for cohort 2.The applicability and opinions of ICU professionals will be measured with a self-composed questionnaire including items to evaluate the fit of the intervention to daily practice and to assess the implementation process. Also, a semi-structured interview with one ICU manager will be performed for deepening the evaluation and describe learned lessons before further dissemination. These measures administered to ICU staff will be performed between October 2019 and March 2020, when the development and implementation of the nurse-led multicomponent intervention to support bereavement in relatives in the IC has been finished*.*

#### Data handling

Data will be collected using Limesurvey (Version 2.06lts Build 160,524) and exported to a secure SPSS database (© IBM SPSS Statistics for Windows, Version 25.0. Armonk, NY: IBM Corp) for management and analysis. All principal investigators will have access to the final study dataset, of which one delegate has control over study codes with links from personal data of the patients and their relatives. To avoid potential bias, the researchers will be blinded from any results that can relate data back to the individual respondents. Personal data will be anonymised.

#### Statistical analysis

Power and feasibility: Baseline (retrospective; t_1_) and follow-up measurements (6 weeks; t_2_ and 6 months; t_3_) will be performed in study samples of 200 relatives per group. These numbers are feasible, starting from a mean of 325 ICU deaths each year in the study setting, given a (2x) 12-month inclusion period, an expected 1.5 loved one per death, and an expected inclusion rate of 50% at 6 weeks and a retention rate of 80% at 6 months. These numbers ensure an effect size of 0.5 with a GPower t-test for the ´difference between two independent means´ (1-β = 95%, *p* < .05, two-tailed, d = .5) [48].

Analyses: Descriptive statistics (e.g., means, medians, or proportions as appropriate) and Student’s T-test between pre-post groups on demographic variables (e.g., gender, age, educational level) and outcome measures (e.g., complicated grief, anxiety, depression, posttraumatic stress, experiences with care) will be used to present noticeable differences between the baseline and intervention groups. Missing data will be handled using the multiple imputation. The scores will be analysed based on original data, and when available, according to established cut-offs. All test will be bilateral and significance will be defined as *p* < .05.

To test the hypotheses repeated measure analyses of variance (ANOVA) will be conducted with time as the within-subject factor (pre- versus post-intervention) and group (cohort 1 and 2) as the between-subject factor. Cohen’s d will be calculated to present effect sizes if applicable. Hierarchical regression analyses will be performed to explore determinants and identify subgroups (such as gender, ethnicity, risk profiles, relationship with patient) of bereaved relatives in the ICU who are at particular risk of developing mental health problems (i.e., those with scores above established cut-offs). Covariates, such as reason of admission, severity of illness, cause of death, bereavement care, time to say goodbye and social support, will be included in the regression model. This model will be adapted for cluster effects to correct for multiple relatives per deceased patient.

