Relatives of deceased ICU patients may develop complicated grief as a consequence of the unpredictable and burdensome situation of losing their loved one. Therefore, complicated grief has been included in the Post Intensive Care Syndrome-Family (PICS-F) framework [17, 18]. Demographic variables such as gender, relationship status, and cultural background, might be associated with complicated grief [19, 20]. In addition, factors related to quality of dying and death, communication of staff, and bereavement care might impact the process of grieving for ICU relatives [21, 22]. However, little is known about the determinants and actual prevalence of complicated grief in bereaved relatives of deceased ICU patients. In two small single-center studies, the prevalence of complicated grief measured by the Inventory of Complicated Grief (ICG) ranged from 5% (two out of 41) [23] to 46% (six out of 13) [24]. A French multi-center study among the relatives of 475 deceased ICU patients reported an incidence of complicated grief assessed by the ICG in half of the respondents at 6 months (52%), which remained unchanged at 12 months [19]. The same study presented a decline in posttraumatic stress symptoms from 6 to 12 months, 44 and 36% respectively, as measured by the Impact of Event Scale-Revised (IES-R). Despite the robust study design, the generalizability of these results to other countries remains unclear due to cultural differences in end-of-life perspectives and subsequent bereavement care. To our knowledge only one study has measured the experiences of bereaved relatives in a Dutch ICU [8]. Among 51 respondents the most reported complaints were sleeping problems, while 86% returned to work and normal activities within 4–16 months. Although this study did not measure complicated grief nor symptoms of stress, it reflects the normal grieving reactions being hard and lasting for a longer period for bereaved relatives in the ICU [8]. Patients could die rapidly, resulting in a dignified death with a low burden of suffering and few signs of discomfort [6]. A Dutch study found that the quality of the dying and death process was perceived as being high by both care-givers and relatives [25]. Therefore, it is important to explore grief and the experiences with the quality of bereavement care in relatives of deceased ICU patients in the Netherlands compared to the existing international findings.

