### Methodology

This study protocol follows the Standard Protocol Items: Recommendations for Interventional Trials (SPIRIT) checklist [33]. The recommended schematic diagram detailing the schedule of enrolment, interventions and assessments is provided in Table 1. The study is non-blinded and non-randomized due to practical issues in the multicomponent intervention elements, which were applied intuitively and in a tailored fit to the relatives by ICU nurses.

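### The named hypothesis test contains only time and cohort, while the abstract and Table 2 promise a covariate-adjusted comparison of these non-randomised cohorts

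*Protocol article*

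**What the plan says.** Under Methodology the protocol states: "The study is non-blinded and non-randomized". The Background (Long-term grief in bereaved relatives) adds: "Demographic variables such as gender, relationship status, and cultural background, might be associated with complicated grief".

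The Statistical analysis section then gives three separate steps.

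- **Description of the cohorts.** The first element is "Descriptive statistics (e.g., means, medians, or proportions as appropriate"), followed by a Student's "T-test between pre-post groups on demographic variables (e.g., gender, age, educational level") and outcome measures. These "will be used to present noticeable differences between the baseline and intervention groups".
- **Test of the hypotheses.** "To test the hypotheses repeated measure analyses of variance (ANOVA) will be conducted with time as the within-subject factor", and cohort as the between-subject factor. No covariate is named.
- **Regression.** "Hierarchical regression analyses will be performed to explore determinants and identify subgroups (such as gender, ethnicity, risk profiles, relationship with patient"). The covariates given as examples, and the correction for several relatives per patient, belong to this model.

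Two other places describe the effectiveness comparison differently. The Methods part of the abstract says that the baseline versus follow-up differences will be regression-adjusted. Table 2, in the Efficacy row, describes the before-after comparison of outcomes as covariate-corrected.

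**The concern.** In a non-randomised before-after study, the intervention effect is only as credible as the handling of differences between the cohorts. The one section that specifies the hypothesis test names no adjustment. The characteristics that the Background links to complicated grief enter only as subgroups for finding relatives at risk.

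A shift in composition is plausible. Under Study cohorts and time points, cohort 1 is the first and second contact persons of patients who died in 2018, approached from March to May 2019. Cohort 2 is all bereaved relatives from a later period, approached at 12 weeks. Only 50% inclusion is expected, and Study status reports that cohort 2 recruitment was postponed because of the pandemic.

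At stake is whether a cohort difference reported as an intervention effect partly reflects who was asked and who answered. There is also an ambiguity about the primary result: a reader cannot tell whether it will be the unadjusted ANOVA or an adjusted regression, and the two may disagree.

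**Working it through.** **1. The plan's own figure.** The protocol gives 200 per group for d = 0.5, 95% power, two-sided 5%. The normal formula gives n = 2 × (1.960 + 1.645)² / 0.5² = 104 per group, and the t-test version 105. So 200 is not the output of that calculation but exceeds it; power at 200 is 99.9%. The figure is close to the feasibility product 325 × 1.5 × 0.50 × 0.80 = 195. Sample size is not the problem here. I use 200 per group below.

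**2. The descriptions side by side.**

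| Place | Cohort comparison |
|---|---|
| Abstract, Methods | adjusted by regression |
| Table 2, Efficacy | corrected for covariates |
| Statistical analysis, hypothesis test | ANOVA, time and cohort only |
| Statistical analysis, regression | for determinants and risk subgroups |

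The first two cannot describe the third. The fourth includes covariates but is not given the task of estimating the cohort effect.

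**3. What an unadjusted test does with a confounding shift.** The two cohorts are different people, so I treat the relevant contrast as a two-group comparison of means, with independent observations and no true effect. With shift b in SD units, the noncentrality is b × √(200/2) = 10b. For b = 0.10 it is 1.0, and the rejection probability is about P(Z > 0.96) + P(Z < −2.96) = 0.17. The t-test values are:

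| Assumed shift (SD) | Share of d = 0.5 | Rejection at 5%, 200 per group |
|---|---|---|
| 0.03 | 6% | 6% |
| 0.05 | 10% | 8% |
| 0.10 | 20% | 17% |
| 0.15 | 30% | 32% |
| 0.20 | 40% | 51% |

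The documents give no size for the shift. For scale: bias = imbalance × predictor effect. A 10-point imbalance in a binary predictor with an assumed effect of 0.3 to 0.5 SD gives 0.03 to 0.05 SD. Reaching 0.10 SD takes, for example, two such 0.05 SD imbalances in the same direction.

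**4. The t-test on categorical demographics.**

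- *Gender.* For 120/200 versus 140/200, the t-test on 0/1 codes gives p = 0.0361 and chi-square p = 0.0360. In 100,000 simulated null comparisons at each of 50%, 60% and 70%, the two tests always reached the same decision.
- *Educational level.* Take an invented three-level example coded 1/2/3, with counts 40/120/40 and 80/40/80. Both mean codes are 2, so t = 0. The expected counts are 60/80/60, and chi-square = 2 × (400/60 + 1600/80 + 400/60) = 66.7 on 2 df, p about 3 × 10⁻¹⁵.

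**5. What non-significance would show.** At 200 per group a true 0.2 SD imbalance (noncentrality 0.2 × 10 = 2) is flagged 51% of the time. With the protocol's own rates, 12 months of deaths yield 325 × 1.5 × 0.50 = 244 relatives and 6 months yield 122; the figure is then 44%.

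**The case against.** The strongest reply is that the protocol does intend adjustment. The abstract and Table 2 say so, gender, ethnicity and relationship with the patient appear in the regression, and its covariate list is open-ended. On that reading the ANOVA sentence is merely condensed, and the exact confounder set belongs in an analysis plan not shown here. Much of this stands. A reader might infer from the Statistical analysis section that the plan as a whole ignores these predictors; the documents do not support that. The absence of a final confounder list is also no fault in an article. What remains is that the section naming the hypothesis test contradicts the other two places.

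A reader might also infer that the t-tests are meant to establish that the cohorts are comparable. The text says only that they present noticeable differences, alongside proportions where appropriate, and nothing makes adjustment depend on their result. Non-significance is therefore a caution for reporting, not an error already made.

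The wrong-test point is small. For gender it has no practical effect. Educational levels are ordered, so a t-test will pick up an upward or downward shift, and the example above was built to give t = 0. Reported proportions would reveal such a pattern.

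Finally, the Background names gender, relationship status and cultural background, not age or education. Treating the latter two as confounders is sensible practice but is not drawn from the document.

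**Conclusion.** The point holds as an internal contradiction with a practical consequence. The hypothesis test as specified is unadjusted, other parts of the protocol promise an adjusted comparison, and in a non-randomised design the unadjusted version leaves cohort differences in the effect estimate. Under the stated assumptions (two-group comparison, independent observations, no true effect), false rejection rises from 5% to 8% for a 0.05 SD shift and to 17% for 0.10 SD. The shift itself is assumed. Several relatives per patient would change these rates.

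One could stack three 10-point imbalances in the same direction, each with a 0.3 to 0.5 SD effect, to reach 0.09 to 0.15 SD, or 18 to 30% of the planned d. I would not rest the point on that: neither the predictor effects nor such a pattern is in the documents.

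The use of a t-test for educational level is a minor correction.

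**What to change.** Reconcile the Statistical analysis section with the abstract and Table 2. Name one between-cohort model per outcome as the test of the hypotheses, adjusted for covariates and corrected for several relatives per patient. Include the relative's gender, relationship to the patient and cultural background, and preferably age and educational level, whatever the baseline comparison shows. The Background's relationship status could mean marital status or the tie to the patient, so the text should say which is meant. If the existing example covariates are carried over, leave out bereavement care, because the intervention is designed to change it.

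For the description of the cohorts, keep the t-test for age, use standardised differences or chi-square for gender, educational level and other categorical variables, and state that non-significance will not be read as balance.

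The cost is analysis wording and a few degrees of freedom. Table 2 lists demographic data for both cohorts without itemising them, so check that each variable above is recorded. Study status says cohort 2 recruitment had not begun, so the change can be fixed before those data arrive.
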